**Primary endpoint:**

- The number and percentage of lesions achieving CR during the study

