**Efficacy:**

1. Rate of complete response (CR) for subjects treated with Rhenium-SCT at 12 months after treatment

MODIFIED VISUAL RECIST (adapted from Response Evaluation Criteria in Solid Tumours) CRITERIA 1.1

- Complete response (CR): disappearance of the target lesion/s
  - Partial Response (PR):  $\geq 30\%$  reduction of the larger initial diameter of the target lesion or sum of the larger initial diameters of the target lesions
  - Progressive Disease (PD):  $\geq 20\%$  increase in the largest initial diameter of the lesion or sum of the larger initial diameters of the target lesions
  - Stable Disease (SD): Neither partial response or progressive disease
2. Quality of Life (Baseline: prior to therapy, 6 months after therapy, and 12 months after therapy) – NMSC QOL questionnaire
  3. Overall response rate (ORR)
  4. Comfort of treatment with Rhenium-SCT using short questionnaire
  5. Cosmetic outcome (measured 12 months after therapy) using VAS. Both subject and clinician assessed.

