### **5.2 Primary Endpoint**

- To assess the number and percentage of lesions achieving CR during the study

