## 9.2 Efficacy Assessments

### 9.2.1 Response Assessments

The rate of Complete Response (CR) for subjects treated with Rhenium-SCT will be calculated at 12 months post-therapy.

An interim analysis is planned once 50% of the subjects have had their 6-month Follow-Up visit.

Treatment responses will be assessed according to the MODIFIED VISUAL RECIST at Baseline and during the Treatment and Follow-Up phases. If an assessment during the study results in Progressive Disease (PD) according to MODIFIED VISUAL RECIST, subjects will be withdrawn and further treated off study.

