## **11.7 Efficacy Analyses**

### **Primary efficacy endpoint: Complete Remission (CR)**

The number of lesions treated per subject will be summarised.

The number (and percentage) of lesions in each category (CR, partial response [PR], stable disease [SD] and progressive disease [PD]) at each timepoint, and the overall best response will be presented. The percentage of lesions achieving CR during the study (i.e., CR is the

best overall response) will be estimated and presented with exact 95% confidence limits overall and by tumour type.

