### Response Criteria

#### Evaluation of target lesions

- \* Complete Response (CR): Disappearance of all target lesions
- \* Partial Response (PR): At least a 30% decrease in the sum of the LD of target lesions, taking as reference the baseline sum LD
- \* Progressive Disease (PD): At least a 20% increase in the sum of the LD of target lesions, taking as reference the smallest sum LD recorded since the treatment started or the appearance of one or more new lesions
- \* Stable Disease (SD): Neither sufficient shrinkage to qualify for PR nor sufficient increase to qualify for PD, taking as reference the smallest sum LD since the treatment started

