**Table 4. Evaluation of best overall response**

| Target lesions
At 12 months | New Lesions at
treated site(s) | Overall response
at 24 months |
|--------------------------------|-----------------------------------|----------------------------------|
| CR                             | No                                | CR                               |
| PR                             | No                                | PR                               |
| SD                             | No                                | SD                               |
| PD                             | Yes or No                         | PD                               |
| CR                             | Yes                               | PD                               |

PR

Yes

PD

CR: complete response; PR: partial response; SD: stable disease; PD: progressive disease

- In some circumstances it may be difficult to distinguish residual disease from normal tissue. When the evaluation of complete response depends on this determination, it is recommended that the residual lesion be investigated (biopsy/Histology) to confirm the complete response status.

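### The primary endpoint counts lesions, but Appendix 5 scores response once per subject, and progressive disease is defined in three different ways

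*Protocol*

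**What the plan says.** **Unit of the endpoint.** The synopsis defines the primary endpoint as "The number and percentage of lesions achieving CR during the study", and section 5.2 repeats it. Section 11.7 tabulates lesions as complete response (CR), partial response (PR), stable disease (SD) or progressive disease (PD), and estimates "The percentage of lesions achieving CR during the study (i.e., CR is the" best overall response).

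**Unit of the scoring rules.** Appendix 5 allows up to three target lesions and adds up their longest diameters. CR is "Disappearance of all target lesions". PR, SD and PD are read from the sum. The Table 5 example records two lesions, one sum and one response category per visit. Section 9.2.1 and the Appendix 5 histology rule also speak of CR for subjects or a patient. The synopsis is looser and mentions either the lesion or the sum.

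**Progressive disease.**
- Appendix 5, response criteria: a rise in the sum, "taking as reference the smallest sum LD recorded since the treatment started or the appearance of one or more new lesions". No site is specified.
- Appendix 5, Table 4: only new lesions at the treated site (column heading "New Lesions at treated site(s").
- Synopsis, efficacy criteria: "increase in the largest initial diameter of the lesion or sum of the larger initial diameters of the target lesions", with no new-lesion criterion.

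**Consequence of PD.** Under section 9.2.1, "subjects will be withdrawn and further treated off study". Section 9.1.4 agrees that such subjects leave the study.

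**The concern.** The site investigator decides response, and Appendix 5 is the guide for doing so. If a site assigns one category per subject and that category is carried to the lesions, the lesion table in section 11.7 is filled with something other than lesion outcomes. In a subject with two or three target lesions, a lesion that has gone is recorded as non-CR because a neighbour remains. The primary numerator then depends on which page the site followed and on how many lesions each subject has.

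The PD conflict raises a different problem. Read literally, the Appendix 5 text makes a new skin cancer anywhere a progression and so a reason to leave the study. That would say nothing about control at the treated site, yet it could stop observation of a target lesion that has not yet been scored CR. Section 11.11 uses available data without imputation, so those later visits could not be recovered.

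**Working it through.** **1. The plan's own example (Table 5).** Baseline longest diameters are 2.3 and 2.4, sum 4.7.
- 6 months: 1.8 + 2.0 = 3.8; (4.7 − 3.8)/4.7 = 19.1%, SD.
- 12 months: 1.6 + 1.5 = 3.1; (4.7 − 3.1)/4.7 = 34.0%, PR.

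Both figures reproduce. Scored lesion by lesion, the reductions are 21.7% and 16.7% at 6 months (both SD) and 30.4% and 37.5% at 12 months (both PR). The two units happen to agree here, so the example does not reveal the mismatch.

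**2. Where they part.** Keep the Table 5 baselines, let the 2.3 lesion clear and leave the 2.4 lesion unchanged. The sum falls (4.7 − 2.4)/4.7 = 48.9%. Appendix 5 gives PR, hence no CR. The endpoint needs 1 CR out of 2 lesions. The subject's category varies with lesion size: if lesions of 0.5 and 0.5 clear and one of 2.4 stays, the sum falls 1.0/3.4 = 29.4%, which is SD. In neither case are the cleared lesions counted.

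**3. Size of the effect on the lesion CR percentage.** Assumptions: each lesion clears with probability p = 0.95, independently, and every lesion takes its subject's category. A lesion in a subject with m target lesions is then scored CR with probability p^m: 0.9500, 0.9025 and 0.8574 for m = 1, 2, 3. The scored rate is Σ(w_m · m · p^m) / Σ(w_m · m), where w_m is the share (or number) of subjects with m lesions. The protocol gives no lesion distribution for this trial, so two mixes are shown.
- *Low.* Section 4.3 cites a study of 52 patients with 55 lesions. Taking this as 49 patients with one lesion and 3 with two: (49 × 0.95 + 6 × 0.9025)/55 = 51.965/55 = 94.5%.
- *High.* 50/30/20% of subjects with one/two/three lesions: (0.5 × 0.95 + 0.6 × 0.9025 + 0.6 × 0.8574)/1.7 = 1.531/1.7 = 90.1%.

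The loss is therefore about 0.5 to 4.9 percentage points. For scale, the distance between threshold and assumed CR rate in the sample size table is 7 to 9 points (97% against 90%; 94% against 85%).

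**4. The PD rules side by side.**

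| Place | Reference for growth | New lesion counts as PD |
|---|---|---|
| Appendix 5, response criteria | smallest sum since treatment | yes, no site limit |
| Appendix 5, Table 4 | not stated | yes, at treated site(s) |
| Synopsis | initial diameter | not mentioned |

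Appendix 5 also takes best overall response as the best category recorded up to 24 months. Table 4, under the same heading, turns a 12-month CR with a new lesion at the treated site into PD. Both cannot hold for the same lesion.

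**5. Who is exposed to the new-lesion wording.** The first response assessment after baseline is at 6 months (Table 2). A lesion scored CR there keeps that CR as its best response. The exposed lesion is one not yet scored CR when a new lesion appears elsewhere and the subject leaves.

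**The case against.** Several points on the other side stand.

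- For a subject with one target lesion, the lesion and subject definitions of CR coincide. If most subjects have one lesion, the distortion is small, as the 94.5% figure shows.
- Sections 5.2 and 11.7 plainly make the lesion the analysis unit, the synopsis wording leaves room for single-lesion scoring, and Table 5 records each lesion's dimensions at each visit. Whether a lesion disappeared can be derived from those data, and a statistical analysis plan could say so. It cannot restore visits lost through withdrawal.
- The choice between initial and smallest diameter as the PD reference affects the sorting of SD and PD, and withdrawal. It does not change whether a lesion has gone.

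A reader might also infer that new skin cancers elsewhere would pull the primary result down sharply: if 10 to 30% of subjects developed one, 95% would become 0.95 × 0.9 = 85.5% to 0.95 × 0.7 = 66.5%. The documents do not support that as an effect on the primary endpoint. The primary analysis uses best overall response, so a recorded CR is not undone by a later lesion elsewhere; under Table 4 only new lesions at a treated site convert a CR. The 10 to 30% rate has no source in the protocol either.

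Nor should a subject-level CR rate be set directly against a lesion-level one as if the gap were the error. The comparison that matters is the lesion percentage under each scoring rule, as worked above.

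**Conclusion.** The contradiction is in the current text. The endpoint and its analysis need a category for each lesion; the only full scoring rules supply one per subject and, followed as written, leave cleared lesions uncounted in subjects with more than one target lesion. With 5% independent failure and inherited categories, a true 95.0% is scored as about 94.5% to 90.1%, depending on an assumed number of lesions per subject. The effect vanishes where every subject has one lesion, and it can be undone from the recorded dimensions provided follow-up continues.

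The three PD definitions, and the clash between best recorded response and Table 4, are a separate inconsistency. Its consequence for the primary endpoint is limited to target lesions not yet in CR when an unrelated new lesion leads to withdrawal. No size can be put on that from the documents. The sample size figures are not in question here; they assume one lesion per subject, where the unit mismatch does not show.

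**What to change.** - In Appendix 5 and the synopsis, state that for the primary endpoint CR is scored for each target lesion separately: that lesion has disappeared, with negative histology if histology was taken.
- Add a lesion-level response category to Table 5 and the eCRF, using the dimensions already recorded. Report any category based on the summed diameters separately, as a subject-level result.
- Record new lesions away from the treated sites as their own item.
- Reconcile the PD and new-lesion wording in the synopsis, the Appendix 5 response criteria, the best-overall-response paragraph and Table 4 with one another, and with the withdrawal statements in sections 9.1.4 and 9.2.1. Which withdrawal rule should apply is for the trial's clinical team; the statistical need is that there be only one.

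The cost is wording in the appendix and synopsis and a change to the eCRF. No new measurement is needed for the lesion-level score.

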#### **Efficacy analysis:**

Primary efficacy endpoint: Complete Response (CR).

The number of lesions treated per subject will be summarised.

The number (and percentage) of lesions in each category (CR, PR, SD and progressive PD) at each timepoint (6 months, 12 months and 24 months) and the overall best response will be presented. The percentage of lesions achieving CR during the study (i.e., CR being the best overall response) will be estimated and presented with exact 95% confidence limits overall and by tumour type.

Secondary efficacy endpoints: Change from baseline in QoL, comfort of treatment, and cosmetic outcomes.

The QoL questionnaire will be scored according to the author's instructions. Change from baseline in score will be calculated. Descriptive statistics will be presented for actual score and change from baseline by timepoint, and overall and by tumour type (BCC/SCC). A mixed model will be fitted with change from baseline as the outcome variable. Baseline score will be included as a covariate and timepoint (6 months/12 months) tumour type, tumour stage as factors. Other relevant prognostic factors assessed at baseline will be included. From the model the adjusted mean change at each timepoint will be obtained and presented with 95% confidence limits. Adjusted mean change will be estimated overall and by tumour type.

Comfort with treatment is being assessed using a questionnaire. The frequency (and percentage) of subjects reporting each option for each question will be presented.

Cosmetic outcome (subject and clinician rated) is being assessed at 12 months and 24 months using a visual analogue score (VAS). Descriptive statistics will be presented overall and by tumour type (BCC or SCC). A mixed model will be fitted with VAS as the outcome variable. Tumour type and tumour stage will be included as factors. Other relevant prognostic factors assessed at baseline will be included. From the model the adjusted mean score will be obtained and presented with 95% confidence limits. Adjusted mean score will be estimated overall and by tumour type.

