**9.1.4 Premature Study Termination**

In case of premature termination during the follow-up period, the investigator shall endeavour to arrange a premature end of study visit and perform examinations according to end of treatment visit. If the subject does not enter the follow-up period, this is the study termination (end of study) visit.

The last follow up visit (24 months) is the regular study termination visit.

The subject will leave the study if:

- they require alternative or further treatments for their lesions; or
- if they have progressive disease (PD).

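### Appendix 5 counts any new lesion as progressive disease in its response criteria but only new lesions at treated sites in Table 4, so a cleared target lesion can be scored CR or PD

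*Protocol*

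**What the plan says.** The protocol describes PD in three places.

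- **Appendix 5, Evaluation of target lesions.** PD is a rise of at least 20% in the sum of longest diameters over the lowest sum seen since treatment, or "the appearance of one or more new lesions". The new-lesion limb names no site. CR, in the same list, requires only that all target lesions have disappeared.
- **Appendix 5, Table 4.** The new-lesion column is headed "New Lesions at treated site(s" (the header closes its bracket there). CR with a new lesion of that kind becomes PD, and CR without one stays CR.
- **Synopsis, Efficacy.** PD is at least a 20% "increase in the largest initial diameter of the lesion or sum of the larger initial diameters of the target lesions". There is no new-lesion limb.

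The primary endpoint is "The number and percentage of lesions achieving CR during the study", and the efficacy analysis explains this as "CR being the best overall response". Appendix 5 defines best overall response as the best recorded up to the 24-month follow-up. Section 9.2.1 also calls for a CR rate at 12 months. Sections 9.1.4 and 9.2.1 take subjects with PD off the study. Appendix 5 leaves response to the site principal investigator.

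**The concern.** The treatment acts on a marked field, and subjects with more than three lesions may enter (Section 7.1). A new basal or squamous cell carcinoma elsewhere on the skin is therefore foreseeable during 24 months of follow-up. Such a lesion says nothing about whether the treated lesion cleared. If it can change the response category, the primary endpoint no longer measures local response alone.

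The outcome would also depend on which part of Appendix 5 each investigator applies, across seven sites and with no central review described. The response criteria work on the subject's sum of target lesions while the endpoint counts lesions, so one new lesion could affect up to three target lesions at once.

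**Working it through.** **Step 1: one patient under each text.** Take a subject whose only target lesion has disappeared and who has a new carcinoma outside the treated field.

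| Text | Result |
|---|---|
| Appendix 5 response criteria | CR limb met and PD limb met; no precedence stated |
| Table 4, target status entered as CR | CR, because the new lesion is not at a treated site |
| Table 4, target status already entered as PD | PD, because the PD row ignores the new-lesion column |
| Synopsis | CR |

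Table 4's site limit helps only if the response criteria have not already produced PD.

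**Step 2: where the primary endpoint is exposed.** The schedule in Table 2 places post-treatment response assessments at 6, 12 and 24 months.

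- *CR already recorded, off-field lesion later.* Under the best-response definition the CR stands.
- *Off-field lesion present at the first visit that would give CR.* For a lesion cleared by 6 months this is the 6-month visit. Scored PD, the subject leaves the study. At least one efficacy item exists, so the subject stays in the ITT set (Section 11.4), and Section 11.11 imputes nothing. The lesion counts as non-CR for good.
- *Off-field lesion at 12 months.* The 12-month and by-timepoint categories can change from CR to PD whether or not CR was recorded earlier.

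**Step 3: reproduce the sample-size claim.** Inputs from Section 11.1 and Table 3: n=120, one lesion per subject, one-sided alpha 0.025. The pass mark r is the smallest count with P(X ≥ r | threshold) ≤ 0.025. Power is P(X ≥ r | assumed CR).

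| Threshold | Assumed CR | Pass mark r | Power |
|---|---|---|---|
| 85% | 94% | 110 | 0.893 |
| 86% | 94% | 111 | 0.816 |
| 87% | 95% | 112 | 0.853 |
| 88% | 96% | 113 | 0.891 |
| 89% | 97% | 114 | 0.930 |
| 90% | 97% | 115 | 0.847 |

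Every row reaches 80%, so the stated claim reproduces.

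**Step 4: sensitivity.** Let q be the share of cleared subjects who have an off-field new lesion at the deciding visit and are scored PD. The protocol gives no value, so q is an assumption. Recorded CR = true CR × (1 − q). With threshold 87% and pass mark 112 of 120:

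| q | Recorded CR (true 95%) | Power | Recorded CR (true 99%) | Power |
|---|---|---|---|---|
| 0 | 95.0% | 0.853 | 99.0% | >0.99 |
| 1% | 0.95 × 0.99 = 94.05% | 0.714 | 0.99 × 0.99 = 98.01% | >0.99 |
| 2% | 0.95 × 0.98 = 93.1% | 0.552 | 0.99 × 0.98 = 97.02% | 0.99 |
| 5% | 0.95 × 0.95 = 90.25% | 0.162 | 0.99 × 0.95 = 94.05% | 0.71 |

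**The case against.** The best defence is that Appendix 5 can be read as a whole. The synopsis is a summary, and the 12- and 24-month visit lists in Section 9.1.3 refer the assessor to Appendix 5. Table 4 keeps target-lesion status and new lesions in separate columns, and its row for CR with a new lesion makes sense only if a new lesion does not itself change the target-lesion category. On that reading the new-lesion limb works through Table 4, at treated sites only, and the patient above is CR.

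Much of this stands. The synopsis is the weaker leg, and the real clash is between the response criteria and Table 4. The word *anywhere* does not appear in the text; it is the literal reading of a clause without a limit. But the harmonised reading has to be inferred. Nothing states it, the 6-month visit list has no pointer to Appendix 5, and Table 4's target-lesion column is labelled for 12 months. The visit that matters most for the primary count is the least well covered.

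A reader might infer that any off-field cancer during follow-up destroys a CR for the primary endpoint. The best-response definition does not support that. A reader might also infer that the study is underpowered. The documents do not support that either: the sample-size claim reproduces, the power losses need an assumed q and literal scoring at every site, and Section 11.1 expects CR close to 100%, where the loss is much smaller. Finally, the error runs against the device and so cannot by itself produce a false claim of efficacy.

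**Conclusion.** The contradiction is real and sits in the current text of Appendix 5, with the synopsis adding a lesser inconsistency. It leaves the response category undefined for a foreseeable patient. For the primary endpoint the exposure is limited to off-field lesions present before any CR has been recorded. The 12-month CR rate, the by-timepoint tables and data lost after withdrawal for PD are also affected.

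The size cannot be taken from the protocol. As a worst case, with one lesion per subject, threshold 87% and every such case scored PD, power at the Table 3 rate of 95% falls from 85% to 71%, 55% and 16% for q of 1%, 2% and 5%. At a true CR of 99% it is 99% and 71% for q of 2% and 5%. These figures show sensitivity and are not forecasts. The planned 120 subjects need no change on this account.

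**What to change.** Reconcile the synopsis definition, the Appendix 5 response criteria and Table 4 to one new-lesion rule for scoring target-lesion response. For the lesion-level CR endpoint, use the treated-site limit that Table 4 already states, and say whether CR or PD takes precedence when both limbs are met. Record new non-melanoma skin cancers elsewhere as a separate item that does not enter the target-lesion category.

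The PD-linked withdrawal text in Sections 9.1.4 and 9.2.1 uses the same term. The sponsor must reconcile it with the chosen definition separately; no exit rule is proposed here.

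The cost is wording in the synopsis and Appendix 5 and one eCRF field. No visits, procedures or subjects are added.

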#### Evaluation of best overall response

The best overall response is the best response recorded from the start of the treatment until the 24 month follow up (taking as reference for PD the smallest measurements recorded since the treatment).

